## Abstract

**Background:**

The success rate of IVF treatment is low. A recent systematic review and meta-analysis found that the outcome of IVF treatment could be improved in patients who have experienced recurrent implantation failure if an outpatient hysteroscopy (OH) is performed before starting the new treatment cycle. However, the trials were of variable quality, leading to a call for a large and high-quality randomised trial. This protocol describes a multi-centre randomised controlled trial to test the hypothesis that performing an OH prior to starting an IVF cycle improves the live birth rate of the subsequent IVF cycle in women who have experienced two to four failed IVF cycles.

**Methods and design:**

Eligible and consenting women will be randomised to either OH or no OH using an internet based trial management programme that ensures allocation concealment and employs minimisation for important stratification variables including age, body mass index, basal follicle stimulating hormone level and number of previous failed IVF cycles. The primary outcome is live birth rate per IVF cycle started. Other outcomes include implantation, clinical pregnancy and miscarriage rates.

The sample size for this study has been estimated as 758 participants with 379 participants in each arm. Interim analysis will be conducted by an independent Data Monitoring Committee (DMC), and final analysis will be by intention to treat. A favourable ethical opinion has been obtained (REC reference: 09/H0804/32).

**Trail Registration:**

The trial has been assigned the following ISRCTN number: ISRCTN35859078

## Background

Only a third of in vitro fertilization (IVF) cycles started end in a pregnancy and one fourth result in a live birth [1,2]. Recurrent IVF implantation failure (two or more failed IVF cycles) is a very distressing experience to patients [3] and increases the financial burden on the couple or service provider. The aetiology of recurrent IVF implantation failure can be broadly attributed to embryonic or uterine factors, but remains unexplained in most cases [4]. A number of interventions have been proposed to improve IVF outcome in such women, but many of these interventions are not evidence-based [5,6]. As a result, there is considerable variation in the approach to investigations and management of recurrent IVF failure [7].

One of the common investigations proposed after recurrent IVF failure is outpatient hysteroscopy (OH). OH is a well-tolerated minimally-invasive procedure, which allows reliable visual assessment of the cervical canal and uterine cavity and provides the opportunity to perform therapy in the same setting [5,8-11]. Intra-uterine pathologies have been shown to be present in 25% of infertile patients [11]. Thus, routine OH prior to IVF has been suggested by a number of investigators to ensure normality of the uterine cavity before embryo transfer [12-19] although this proposition has not been tested in a randomised setting.

In order to capture all existing evidence on whether OH could improve the outcome of the subsequent IVF cycle in patients who have experienced recurrent IVF implantation failure, we conducted a systematic review and meta-analysis [20]. We identified two randomized studies [21,22] which examined the impact of OH on the outcome of the subsequent IVF cycle after two or more failed IVF attempts. Both studies included patients with normal uterine cavity on hysterosalpingography. The researchers in both studies performed the hysteroscopy as an outpatient procedure, used a 5-mm hysteroscope with a 30° view, reported no complications and discharged patients within one hour after the procedure. Both studies showed a statistically significant improvement in the clinical pregnancy rate in the group who had OH (pooled RR = 1.57, 95%CI 1.29-1.92, p < 0.00001). The number needed to treat with OH in order to achieve an additional clinical pregnancy in the study populations was 7 (95%CI 5-12). The miscarriage rate was not statistically different between the OH and control groups [20].

However, there were deficiencies in the quality of these 2 randomised studies. For example, one study [22] did not report adequate concealment of allocation. Lack of concealment can exaggerate effect size by up to 41% [23]. In addition, only one of the studies [22] reported live birth rate per IVF cycle started. Furthermore, both studies were single-centre randomised studies, leading to limited generalisability of their findings. A well designed, adequately powered, allocation concealed multi-centre trial is therefore needed to address this research question.

## Methods and design

### Objective

In the proposed trial we will evaluate whether performing an OH prior to starting an IVF cycle improves the likelihood of achieving a live birth after the IVF cycle in women who have experienced two to four IVF implantation failures.

### Design

A prospective, allocation concealed, single blind, multi-centre randomised trial with health economic evaluation.

### Outcomes

The primary outcome is live birth rate (beyond 24 weeks gestation) per IVF cycle started. The secondary outcomes are embryo implantation rate, pregnancy rate per IVF cycle started, clinical pregnancy rate per IVF cycle started and miscarriage rate per pregnancy achieved

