#### Statistical analysis

The analysis will be by intention to treat, and will be carried out in the following four steps:

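### Miscarriage is defined only per pregnancy achieved, a subset that OH is expected to enlarge, so its comparison between arms is not protected by randomisation

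*Protocol article*

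**What the plan says.** All places are in the protocol article.

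- **Outcomes.** The primary outcome is on a cycle basis: "The primary outcome is live birth rate (beyond 24 weeks gestation) per IVF cycle started". Pregnancy and clinical pregnancy have the same denominator. The secondary list ends with "clinical pregnancy rate per IVF cycle started and miscarriage rate per pregnancy achieved". Miscarriage is given on no other denominator.
- **Statistical analysis.** "The analysis will be by intention to treat". Step 2 compares dichotomous outcomes between groups by Fisher's exact or chi-square test, with p-values and 95% confidence intervals. No exception is made for miscarriage. Step 2 also rests the success or failure of the study on live birth alone.
- **Background.** The two earlier trials are said to have found more clinical pregnancies after OH, with this summary estimate: "pooled RR = 1.57, 95%CI 1.29-1.92, p < 0.00001". On losses the section reports: "The miscarriage rate was not statistically different between the OH and control groups". No miscarriage rate is given. On IVF in general it says: "Only a third of in vitro fertilization (IVF) cycles started end in a pregnancy". It puts live birth at a quarter of cycles.

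**The concern.** The reason for the trial is that OH may turn failed cycles into pregnancies. If it does, the OH arm's miscarriage denominator contains women whose counterparts in the control arm did not conceive and are not counted. Those added pregnancies need not carry average risk. The Background puts intra-uterine pathology at 25% of infertile patients, and the OH procedure includes an attempt to treat small lesions, so the added pregnancies may come disproportionately from women with treated pathology.

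If the added pregnancies are more fragile than average, OH will seem to raise miscarriage although no pregnancy that would have occurred anyway was harmed. If they are more robust, a real harm can be hidden. Step 4 of the analysis adjusts only when randomisation leaves the groups unbalanced, which does not deal with selection after randomisation.

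Miscarriage is the only harm-type item in the Outcomes list, so readers are likely to use it to judge whether OH is safe for a pregnancy.

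**Working it through.** The article states no expected figure for miscarriage, so there is none to reproduce. Its recruited number does reproduce: 360 / 0.95 = 378.9, hence 379 per arm.

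**Inputs**
- 379 women per arm (Number of participants), assuming that each starts one cycle.
- Control pregnancy rate 1/3 (Background; a general IVF figure, not specific to this population).
- Effect on pregnancy, two cases: +10 points (assumption), or RR 1.57 (Background; reported for clinical pregnancy, applied here to any pregnancy as an assumption).
- Loss risk of 20% in women who would conceive in either arm, unchanged by OH (assumption).
- Loss risk of 10%, 20% or 40% in the added OH pregnancies (assumption).

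**Denominators**
- Control: 379 × 1/3 = 126.
- OH, +10 points: 379 × 0.433 = 164.
- OH, RR 1.57: 1/3 × 1.57 = 0.523, and 379 × 0.523 = 198.

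**Formulae.** Let p_C and p_T be the pregnancy rates, r the usual loss risk and x the risk in the added pregnancies.
- OH miscarriage per woman: p_C·r + (p_T − p_C)·x
- OH miscarriage per pregnancy: the same divided by p_T
- Control: p_C·r per woman, r per pregnancy

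Example (RR 1.57, x = 40%): per woman 0.333 × 0.20 + 0.190 × 0.40 = 0.143; per pregnancy 0.143 / 0.523 = 27.3%.

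| Effect on pregnancy | x | Per pregnancy, control vs OH | Shift (points) | Per woman, control vs OH |
|---|---|---|---|---|
| +10 points | 10% | 20% vs 17.7% | -2.3 | 6.7% vs 7.7% |
| +10 points | 20% | 20% vs 20% | 0 | 6.7% vs 8.7% |
| +10 points | 40% | 20% vs 24.6% | +4.6 | 6.7% vs 10.7% |
| RR 1.57 | 10% | 20% vs 16.4% | -3.6 | 6.7% vs 8.6% |
| RR 1.57 | 20% | 20% vs 20% | 0 | 6.7% vs 10.5% |
| RR 1.57 | 40% | 20% vs 27.3% | +7.3 | 6.7% vs 14.3% |

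In every row OH harms no pregnancy that would have occurred without it.

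**A base risk taken from the article.** One third pregnant and one quarter with a live birth imply 1 − 0.25/0.333 = 25% of pregnancies lost. This counts every loss as a miscarriage. With +10 points and x = 40%:
- Per pregnancy: (33.3 × 0.25 + 10 × 0.40) / 43.3 = 28.5% against 25%.
- 95% CI half-width: 1.96 × √(0.25 × 0.75/126 + 0.285 × 0.715/164) = 10.2 points.
- z = 3.5 / (10.2/1.96) ≈ 0.7.
- Per woman: 12.3% against 8.3%, ratio 1.48. The standard error is √[(0.083 × 0.917 + 0.123 × 0.877)/379] = 2.2 points, so z ≈ 1.8.
- On the per-woman scale the outcomes add up: pregnancy 33.3% vs 43.3%, loss 8.3% vs 12.3%, live birth 25.0% vs 31.0%.

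**The case against.** **The remedy can look worse than the problem.** In the last example the per-woman rate gives the larger apparent harm (z about 1.8 against 0.7). Even when the added pregnancies carry average risk, it rises (6.7% to 8.7% or 10.5%) while the per-pregnancy rate stays level. Used alone, it would penalise OH for producing pregnancies. This stands, and it is why the rate must be shown beside live birth and not replace one misreading with another.

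**Bias is not shown.** A reader might infer that the pregnant women in the two arms are certain to differ. The article does not establish that. The loss risks above are assumptions, and the earlier trials found no significant difference in miscarriage. That finding does not demonstrate equality, but it lends no support to fragile added pregnancies. In the 25% example the shift is about a third of the confidence interval half-width.

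**The plan does not break intention to treat as it uses the term.** A reader might infer a contradiction with the Statistical analysis section. Withdrawal of Subjects describes the principle as analysing women in their allocated group, and a per-pregnancy rate does keep them there. The weakness lies in the causal reading.

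**The rates can be linked.** It is tempting to say that miscarriage cannot be reconciled with live birth. It can: the listed pregnancy rate per cycle multiplied by miscarriage per pregnancy gives miscarriage per cycle, provided pregnancy means the same event in both. That recovers the point estimate, but the planned test would still be on the pregnant subset.

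**Safety is covered elsewhere.** Adverse event rates come from the hysteroscopy findings chart (OH arm), and the DMC reviews serious adverse events. Miscarriage is the only harm-type item within the Outcomes list, not in the whole plan.

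**A second denominator could be left to the SAP.** True, but the article itself fixes the denominator it gives, and Step 2 covers it without qualification.

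**Conclusion.** The point holds in limited form. Miscarriage is defined only within a subset formed after randomisation, the trial's own rationale expects OH to enlarge that subset, and the plan would test it as an ordinary comparison between groups. Neither a difference nor its absence can then be attributed to OH by virtue of randomisation.

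Under the assumed loss risks, composition alone shifts the OH rate by -2.3 to +4.6 points (+10 points of pregnancy) or by -3.6 to +7.3 points (RR 1.57). It shifts nothing if the added pregnancies carry average risk.

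The consequence is modest. One secondary outcome is affected; the sample size and the success criterion do not depend on it, and the primary outcome already counts pregnancy losses as failures. What is limited is the conclusion that may be drawn about miscarriage.

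**What to change.** 1. Add miscarriage for all women randomised as the intention-to-treat comparison. Per cycle started would match the live-birth denominator in Outcomes; the two coincide only if every randomised woman starts a cycle, so name the one chosen.
2. Show pregnancy, miscarriage and live birth together on that denominator, by arm.
3. Keep miscarriage per pregnancy, which clinicians know, and label it as a descriptive comparison within a non-randomised subset.
4. State with the new rate that it rises whenever more women conceive, so that it is read beside live birth and not alone as evidence of harm.

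The cost is wording and one extra table row, with no new data. The real downside is the one in item 4.

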### Inclusion criteria

Women undergoing an IVF (with or without intracytoplasmic sperm injection) treatment cycle who have had between two to four fresh IVF cycles ending in an embryo transfer but no implantation are eligible to participate in the trial. For the purpose of this study, implantation is defined as the presence of an intra-uterine gestational sac showing fetal cardiac pulsations 4 - 5 weeks after embryo transfer.

### Exclusion criteria

Women who had less than two or more than four failed fresh IVF cycles ending in an embryo transfer, women aged 37 years or more at the time of randomisation, women who have had a hysteroscopy within 2 months of randomisation, the presence of submucous or intramural uterine fibroids distorting the uterine cavity or untreated tubal hydrosalpinges and a body mass index (BMI) above 35 (36 or higher).

The rationale for not including women aged 37 years and older is that the primary factor in IVF failure in this age group is related to embryo quality, which is unlikely to be corrected by uterine or endometrial manipulation. Submucous and intramural uterine fibroids distorting the uterine cavity and untreated tubal hydrosalpinges are known causes of IVF cycle failure and require specific treatment aimed at reversing their detrimental effects. Patients with a history of fibroids removal or treatment of tubal hydrosalpinges will not be excluded.

### Randomisation

Third party, distant, internet-based randomisation will be used to ensure randomisation and allocation concealment. Participants will be randomised online via a secure internet facility in a 1:1 ratio through a third party independent Integrated Trial Management System (MedSciNet Clinical Trial Framework) that has been designed, developed and delivered according to ISI9001-2000 standards and compliant with FDA CFR21:11 requirements. A "minimisation" procedure using a computer-based algorithm will be used to avoid chance imbalances in important stratification variables, such as age, BMI, number of previous failed IVF cycles and basal FSH level (as dichotomous variables). The randomised allocation will not be given until all eligibility and stratification data have been given.

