### Blinding

The trial will be single-blinded, where the embryologists involved in the embryo transfer procedure are blinded to group allocation, thus minimising performance bias. Measurement bias in unlikely to interfere with the trial analysis and result due to the objective nature of the primary outcome (live birth).

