**Figure 1 F1:**
[figure not shown]
**Participants flow in the study**.

If the woman agrees to participate in the trial, further information and instructions relating to the trial are given [see Additional file 1], and she is requested to sign the trial consent form [see Additional file 2] by a clinician. Contact and baseline data are collected in the electronic Integrated Trial Management System (ITMS) [see Additional file 3]. Each woman will be randomised to either the intervention or the control group.

All women are given instructions to notify the clinic nurse by telephone at the start of their menstrual cycle to inform her of their intention to start treatment in that cycle. When the nurse receives the call from the woman, the nurse will randomise the patient, and if the woman is allocated to the OH group, will book an OH within 14 days of the beginning of menstruation. Women randomised to OH arm will attend the respective Unit for OH within 14 days of the beginning of menstruation. They will then be expected to start the IVF process according to a standard controlled ovarian stimulation protocol [24]. Women randomised to the control group will start the IVF process according to a standard controlled ovarian stimulation protocol without OH.

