### Trial intervention

#### Outpatient hysteroscopy (OH)

The OH procedure will be performed in the first two weeks of the menstrual cycle by named surgeons in each of the participating centres (Box 1):

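### Centre is not named as a minimisation factor and the primary comparison is unadjusted, so a small chance imbalance between centres would stay in the live birth result

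*Protocol article*

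**What the plan says.** The trial is described under Design as "A prospective, allocation concealed, single blind, multi-centre randomised trial with health economic evaluation". The article does not give the number or size of centres.

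The minimisation factors appear twice:

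- Randomisation section: "important stratification variables, such as age, BMI, number of previous failed IVF cycles and basal FSH level (as dichotomous variables".
- Abstract, Methods and design: "important stratification variables including age, body mass index, basal follicle stimulating hormone level and number of previous failed IVF cycles".

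The four factors are the same in both places, and centre is in neither. Allocation is central: "Participants will be randomised online via a secure internet facility in a 1:1 ratio". At the clinic, "the nurse will randomise the patient". Under Blinding, the only people named as blinded are embryologists: "the embryologists involved in the embryo transfer procedure are blinded to group allocation".

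Step 2 of the statistical analysis compares dichotomous outcomes by chi-square or Fisher's exact test and lets live birth alone decide success. Step 4 brings in logistic regression only as a secondary analysis, and only if the groups turn out unbalanced. If the two analyses disagree, the unadjusted one carries more weight.

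**The concern.** Live birth after IVF plausibly depends on the centre, through its laboratory, its transfer practice and the patients it sees. Minimising on four patient characteristics does not balance the arms within a centre. If centre is left out, one arm can by chance draw more of its women from the more successful centres.

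The planned analysis would not correct this. The test that decides success ignores centre, and an adjusted analysis that disagreed would rank below it. At stake are a little precision and a conditional shift in the estimate that could easily be avoided, since centre is known when each woman is randomised and within-centre balance cannot be restored afterwards.

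**Working it through.** **1. The plan's own figures (Number of participants).** Inputs are 25% v 35%, two-sided 5% alpha and n = 360 per arm.

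- Standard error of the difference: √[(0.25×0.75 + 0.35×0.65)/360] = √(0.415/360) = 0.0340, or 3.4 points.
- Null standard error: √(2×0.30×0.70/360) = 0.0342.
- Power: Φ[(0.10 − 1.96×0.0342)/0.0340] = Φ(0.97) = 83.5%, which meets the stated target of over 80%.
- Dropout: 720/0.95 = 757.9, so 758.

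The stated sample size reproduces and does not depend on the point made here.

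**2. Balance within a centre if centre is not a factor.** Centre sizes are assumed. Treating allocation within a centre as a fair coin:

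- 40 women: P(split of 60:40 or worse) = 2×P[Bin(40, 0.5) ≤ 16] = 26.8%.
- 20 women: 2×P[Bin(20, 0.5) ≤ 8] = 50.3%.

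A simulation of minimisation (758 women, four binary factors, preferred arm chosen with probability 0.8, 300 runs, equal centres) gave these differences between arms within a centre:

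| Centres (assumed) | Without centre: mean; 95th percentile | With centre: mean; 95th percentile |
|---|---|---|
| 4 | 9.6; 24 women | 1.6; 4 women |
| 8 | 7.5; 18 women | 1.7; 4 women |
| 12 | 6.0; 15 women | 1.7; 4 women |

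**3. Effect on the overall comparison.** Let s be the SD of live birth rates between centres, assumed to be 5 to 10 points. The SD of the chance shift in the arm difference is s×√(4/758) = s×0.0726.

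- s = 5: 0.36 points.
- s = 10: 0.73 points.

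In the simulation, with centre rates spread evenly from 15% to 35% (assumed), the SD of the shift was 0.4 to 0.6 points without centre and about 0.1 with it.

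**4. Effect on power.** The share of outcome variance due to centre is s²/(0.30×0.70).

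- s = 5: 0.0025/0.21 = 1.2%. Effective n = 360/(1 − 0.012) = 364 per arm, power 83.9%.
- s = 10: 0.01/0.21 = 4.8%. Effective n = 360/(1 − 0.048) = 378 per arm, power 85.2%.

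**5. Where the gain comes from.** Adjusting for centre removes the shift even when the arms are unequal within a centre. A 60:40 split costs only 1 − 4×0.6×0.4 = 4% of that centre's information. So most of the power gain comes from the adjustment and little from the balancing.

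**6. If centre is already a factor.** The unadjusted standard error would still contain the centre variance that the balancing has removed. It would be too large by a factor of 1/√(1 − 0.012) = 1.006 to 1/√(1 − 0.048) = 1.025, or about 0.6% to 2.5%. The analysis therefore merits the change in either case.

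**The case against.** **The lists are open.** Both lists are worded as examples, and a journal article condenses the full protocol. A reader might infer that centre is definitely excluded; the text does not say so. Likely exclusion is as far as it goes: the same four variables are named twice as the important ones, and the body calls them dichotomous, which centre could be only with exactly two centres. The abstract repeating the body is weak additional evidence. This part of the objection stands.

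**Surgeon skill.** Because hysteroscopy is done "by named surgeons in each of the participating centres", a reader might infer that operator skill gets mixed into the comparison. It does not. Controls have no hysteroscopy, so operator skill exists only in the intervention arm and is part of the intervention's effect. Only differences in underlying centre success rates matter here.

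**No bias.** A reader might also infer a biased trial. The imbalance is random, and the unadjusted standard error already includes it: 0.73²/3.40² = 0.53/11.5, about 4.6%, close to the 4.8% share above. Type I error and interval coverage are not harmed by leaving centre out of both the allocation and the analysis. This stands and limits the point to precision.

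**Step 4 could cover centre.** It could, if centre counts as an unbalanced prognostic factor. But that analysis is conditional and secondary, and ranks below the unadjusted result. It therefore does not remove the shift from the deciding comparison.

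**Predictability.** Balancing within centres makes the next allocation somewhat easier to guess locally, where a nurse randomises and only embryologists are named as blinded. The article mentions no random element, though the full protocol may. The change is therefore cheap but not free.

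**Conclusion.** The point holds as a minor one. Centre is not named in either list and is probably not a factor, and the primary comparison takes no account of it. Taking account of it would remove a chance shift with an SD of about 0.4 to 0.7 points, against a standard error of 3.4 points and a target difference of 10 points. Power at 360 per arm would rise from 83.5% to about 84–85%.

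These sizes rest on an assumed between-centre SD of 5 to 10 points and, for the within-centre splits, on assumed numbers and sizes of centres. The article gives none of these. The conclusion of the trial is not threatened, and the sample size stands. The case for acting is that the change is cheap and that allocation cannot be rebalanced later.

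**What to change.** - State the full list of minimisation factors and say whether centre is one.
- If it is not, add centre to the web-based minimisation and specify a random element so that local staff cannot readily predict the next allocation.
- In either case, replace the unadjusted primary comparison of live birth with one that accounts for centre, for example logistic regression or a Mantel-Haenszel analysis, with a prespecified rule for pooling very small centres. Keep the chi-square or Fisher test as supportive.
- Amend Steps 2 and 4 to match, since they now make the unadjusted result primary and give it precedence.

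The cost is a configuration change in the randomisation system and a rewrite of the primary analysis text. No extra women or data are needed, and the totals of 720 and 758 stay as they are. The one real downside is slightly greater predictability of allocation within centres, which the random element limits but does not abolish.
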